**Fig. 1 Fig1:**
[figure not shown]
CONSORT flow diagram

### Recruitment

Participants are recruited online, using social media platforms to promote the study. By clicking the enrolment link, participants read the study information section and the informed consent form, which can be signed digitally, by agreeing to the terms and the conditions of the study. Participants are queried about the criteria for inclusion and exclusion, following which eligible individuals are selected through randomization. The planned flow of participants can be consulted in Figure 2.

**Fig. 2 Fig2:**
[figure not shown]
Planned flow of participants. Note: ATQ-Automatic Thoughts Questionnaire; BEAQ-Brief Experiential Avoidance Questionnaire; CSQ-8- Client Satisfaction Questionnaire-8; GAD-7-Generalized Anxiety Disorder-7; GHQ-12-General Health Questionnaire-12; IUS-Intolerance of Uncertainty Scale; OBQ-44-Obsessive Beliefs Questionnaire-44; ØCD - OCD prevention program; OCI-R-Obsessional Compulsive Inventory – Revised; PHQ-9-Patient Health Questionnaire-9; RSA-Resilience Scale for Adults; WHOQOL-BREF-WHO Quality of Life – BREF

Therapists are from the clinical psychology master's program. We recruited four terminal year students following an introductory meeting on the purpose of the study and the procedures involved. The expected time expenditure for the therapists will be 9 hours per week. Before implementation, all therapists will have participated in a training supported by the study coordinator.

### Inclusion and exclusion criteria

Participants are included if they are of legal age (above 18). We include participants who have an OCI-R [10] score at or above the cut-off point on the OCD subscale (≥ 12). Exclusion criteria are as follows: (1) clinically diagnosed OCD, (2) current psychiatric/psychotherapeutic treatment, (3) a personality disorder diagnosis, and (4) suicidal ideation.

### Procedure and randomization

Inclusion and exclusion criteria are verified based on the screening form completed by the participants. Eligible participants are randomly allocated to one of the two conditions in a 1:1 ratio. Randomization is conducted by a member of the research team, using the online tool, randomizer.org. The allocation sequence is generated through a computer-generated random sequence for the two study conditions. The following study personnel will remain blind to group allocation until the final data analyses are completed: principal investigator, data managers, and outcome assessors.

### Outcome measures

For participants, the baseline assessment will take place after randomization and include a set of validated questionnaires.

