## Methods

### Study design and ethical aspects

We will conduct a single-blind (blinded outcome assessors), randomized (1:1), controlled, parallel-group, superiority trial comparing the ØCD prevention program with a control group (waitlist) for adults at risk of OCD. The study is registered on clinicaltrials.gov (ID: NCT06262464). All quality and safety aspects will be regularly monitored by an external party: the University Ethical Review Board, and by the financing authority of the project (National Authority for Scientific Research). The study has been approved by the University Ethical Review Authority (937/28.11.2023). Potential protocol modifications will be described in detail on clinicaltrials.gov. We used the SPIRIT reporting guidelines [6].

Participants will be asked to provide informed consent before baseline assessment. They will receive detailed information about the study and their right to withdraw from the study without the obligation to give reasons. We do not expect major relevant risks for participants during the study, or after the study is completed. The time burden for the participants will be a reasonable amount. The data collection and storage will be conducted according to GDPR legislation, and all personal data will be securely stored on the University’s encrypted servers, following the set data management guidelines.

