### Primary outcome measures

#### Obsessional Compulsive Inventory - Revised (OCI-R; [10])

OCI-R is a self-report questionnaire of 18 items, and it measures OCD symptoms across six subscales: washing, checking, neutralising, obsessing, ordering, and hoarding. OCI-R was used in the initial screening of eligible participants, where the OCD subscale (which excludes the hoarding component) was used to determine participants who are at risk of developing OCD symptoms (cut off point (≥ 12). For the present study, the reduction in OCI-R OCD subscale assessment is the primary outcomes.

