### Statistical analyses

#### Data analysis

Demographic and clinical data will be reported as means and SDs for continuous parametric data, medians, and ranges for non-parametric data, and frequencies and percentages for categorical data. Only two authors will have access to the final trial dataset. To illustrate participant flow, we will report results in a CONSORT diagram. Data analysis will be conducted using SPSS for Windows version 25. Given the anticipated dropout rate, mixed models will be employed as the most suitable statistical method. This approach is well-suited for analyzing repeated measures, accounting for the dependency between observations and handling missing data effectively. Mixed models will be adjusted for baseline values of the repeated measures. Descriptive statistics will be generated to summarize the means and proportions of baseline clinical and demographic variables across treatment conditions, allowing for the assessment of potential imbalances. Fixed effects in the model will include time, treatment, and their interaction. In cases of missing data, these variables will also be included as fixed effects. The significance of the time*treatment interaction p-values for various outcome measures will be assessed using the Benjamini–Hochberg procedure (two-sided p < 0.05). Time will be treated categorically, with the first post-baseline measurement serving as the reference category. To address the correlation among repeated measurements, a first-order autoregressive (AR (1)) structure will be imposed on the residuals. Furthermore, the interaction effect between time and group will be explored by analyzing estimated marginal means at different time points. We anticipate a significant interaction effect between time and group, signifying differential changes in scores over time between the two treatment conditions. Specifically, we expect a more pronounced decline in scores over time in the prevention group compared to the control group. To assess the statistical significance of improvements in the treatment conditions, a least significant difference test will be conducted with estimated marginal means to compare changes between groups. Linear mixed models are expected to reveal a statistically significant decline in the prevention condition from pretest to post-test, with no significant differences between post-test and follow-up measures. To facilitate comparisons with other studies, Cohen’s d statistic will be calculated to determine within-group effect sizes. In cases where the proportion of missing data exceeds 10%, maximum likelihood imputations will be performed based on demographics and pretreatment scores. Additionally, the proportions of dropouts and diagnostic incidence (from pre-test to follow-up) in the two treatment groups will be compared using the chi-square test.

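### Self-report baseline questionnaires follow randomization with no stated concealment of the arm, so the covariate in the mixed models can be affected by allocation

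*Protocol article*

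**What the plan says.** All references are to the protocol article.

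- **Order of steps.** Under Procedure and randomization, eligibility is checked from a screening form that participants complete, and eligible people are then allocated. Under Outcome measures, "the baseline assessment will take place after randomization and include a set of validated questionnaires".
- **Blinding.** Study design and ethical aspects describes a "single-blind (blinded outcome assessors), randomized (1:1), controlled, parallel-group, superiority trial". Procedure and randomization adds: "The following study personnel will remain blind to group allocation until the final data analyses are completed: principal investigator, data managers, and outcome assessors". Neither place mentions participants.
- **Comparator.** The trial is described as "comparing the ØCD prevention program with a control group (waitlist) for adults at risk of OCD".
- **Measurement.** "OCI-R is a self-report questionnaire of 18 items", and the assessments are completed online.
- **Use in the analysis.** Under Data analysis, "Mixed models will be adjusted for baseline values of the repeated measures". The OCI-R outcome is worded as a reduction, and Cohen's d is to be calculated within groups.
- **What exists before allocation.** "OCI-R was used in the initial screening of eligible participants", with a cut-off of 12 or more on the OCD subscale. The text does not name this score as the model baseline, and it describes no pre-randomization PHQ-9, GAD-7 or secondary scale.

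**The concern.** Baseline adjustment is safe when allocation cannot have influenced the covariate. Here the article fixes an order in which it can. Someone who already knows that they will start the programme, or that they must wait, may answer symptom questionnaires differently. Blinded assessors offer no protection when the participant is the one reporting. A difference created in this way is then treated by the model as a pre-existing difference between the arms and adjusted away, which moves the estimated effect.

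The second route is loss. A person disappointed by the waitlist can leave before giving any baseline, so the set of people with a baseline value may differ by arm for reasons linked to allocation.

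The three scales that the abstract names as primary (OCI-R, PHQ-9, GAD-7) are exposed, and for two of them no pre-randomization score is described against which a shift could be checked.

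**Working it through.** The article gives no figure on this point, so there is none to reproduce. The first step is a reading of the text; the second is an illustration.

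**1. Sequence as stated.** Screening form (including OCI-R), then allocation, then baseline questionnaires, then programme or waitlist, then post-test and follow-up. Consent is required before baseline, which is compatible with this order. No statement places disclosure of the arm after baseline. The participant-flow figure is not shown in the text reviewed.

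**2. Size if the arm is known.** Let g be the shift in reported baseline in one arm, in SD units, and let ρ be the slope of outcome on baseline (equal to the correlation when both have unit SD). Suppose the shift affects the baseline answers only. Then:

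- bias in the baseline-adjusted arm difference = −ρ × g when the programme arm's baseline is shifted upward, with the sign reversed for the opposite shift;
- bias in an unadjusted change from baseline = the full g.

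Inputs: 100 per arm and d = 0.3 come from the Sample size section. Both ρ and g are assumptions; the article gives neither. Simulated ANCOVA at a single post-test: 4,000 runs, unit SD, true effect 0, two-sided 0.05.

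| ρ | g (SD) | −ρ × g | Simulated bias | Size as share of d = 0.3 | Simulated type I error |
|---|---|---|---|---|---|
| 0.5 | 0 | 0 | −0.002 | 0% | 0.048 |
| 0.5 | 0.1 | −0.05 | −0.052 | 0.05/0.3 = 17% | 0.067 |
| 0.5 | 0.2 | −0.10 | −0.099 | 0.10/0.3 = 33% | 0.126 |
| 0.5 | 0.3 | −0.15 | −0.146 | 0.15/0.3 = 50% | 0.210 |
| 0.7 | 0 | 0 | 0.000 | 0% | 0.047 |
| 0.7 | 0.1 | −0.07 | −0.068 | 0.07/0.3 = 23% | 0.103 |
| 0.7 | 0.2 | −0.14 | −0.142 | 0.14/0.3 = 47% | 0.281 |
| 0.7 | 0.3 | −0.21 | −0.211 | 0.21/0.3 = 70% | 0.538 |

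The rows with g = 0 stand for a baseline taken before the arm is known: no bias and a nominal error rate.

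The formula concerns the adjusted arm difference at a visit. In a contrast between two post-baseline visits, the same bias would cancel if the baseline slope were equal at both.

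**3. Would the data show it?** With 100 per arm, the standard error of a baseline mean difference is √(2/100) = 0.141 SD. Shifts of 0.1, 0.2 and 0.3 SD are 0.7, 1.4 and 2.1 standard errors. Most of that range looks like chance imbalance, so a baseline table would not settle the matter. For OCI-R, screening and baseline scores can be compared by arm; for PHQ-9 and GAD-7 no such check is described.

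**The case against.** The strongest reply is that the article never says when participants learn their arm. The list of blinded people covers study personnel, so the absence of participants from it says nothing about when they are told. If disclosure follows the questionnaires, a post-randomization baseline is as good as a pre-randomization one for this purpose. This stands, and it makes the reporting bias conditional. It does not remove the point, because the stated order permits the problem and no stated safeguard prevents it.

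A reader might infer more than the text supports in four ways:

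- **That participants were in fact unblinded at baseline.** This is an inference from the single-blind design and the waitlist; it is not stated. Nor does a post-randomization covariate by itself undo randomization. It does so only if allocation influenced it.
- **That every efficacy analysis is affected.** The chi-square test of diagnostic incidence has no baseline covariate, and the MANOVA in the abstract has no stated adjustment.
- **That people without a baseline are certain to be excluded.** Data analysis plans maximum likelihood imputation, from demographics and pretreatment scores, when more than 10% of data are missing. Whether this covers a missing baseline, and what happens at or below 10%, is unclear. Exclusion is possible but is not the stated plan.
- **That the size is established.** Slope and shift are both assumed, and the formula supposes that only the baseline answers move. If altered reporting persists to post-test, the net bias differs. Reordering would not remove that part, since the later OCI-R is self-report too.

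**Conclusion.** The point holds in conditional form. The article places self-report baseline questionnaires after allocation and uses them as covariates in the mixed models, without saying that the arm is withheld meanwhile. The covariate, the pre-post change and the within-group d can therefore be affected by allocation, and loss before baseline can differ by arm.

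If the arm is known at baseline, the bias in the adjusted effect is about 0.05 to 0.21 SD in either direction, or 17% to 70% of the planned d of 0.3. This rests on an assumed slope of 0.5 to 0.7, an assumed shift of 0.1 to 0.3 SD and a shift confined to baseline. If disclosure follows baseline, the reporting bias largely vanishes. Sample size and power figures are not changed by this point.

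It deserves action while inclusion is open, because no pre-randomization PHQ-9 or GAD-7 is described and none can be recovered later.

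**What to change.** 1. **People not yet randomized** (up to 200 − 121 = 79, counting from the number given at submission): complete the full baseline battery before randomization, or at least before the arm is disclosed, and state this in the protocol.
2. **OCI-R mixed model:** use the screening OCD-subscale score as the baseline covariate for all participants, so that one measurement occasion serves throughout. Using screening scores for the first 121 and a new baseline for the rest would mix two occasions in one model. Include all randomized participants.
3. **PHQ-9, GAD-7 and secondary scales:** state when the arm was disclosed to those already randomized (121/200 = 60.5% of the target at submission). If it was before baseline, do not rely on their post-randomization baseline; report the analysis adjusted for screening OCI-R alongside the one adjusted for the scale's own baseline.

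**Cost.** Some batteries will be completed by people who then do not proceed. The screening score is restricted to 12 or more, so as a covariate it gives somewhat less precision. Allocation is done by a team member with an online randomizer, while Qualtrics is named only for the assessments, so the change is to the team's order of work as well as to the survey. For those already randomized, the change is to the analysis only.

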### Primary outcome measures

#### Obsessional Compulsive Inventory - Revised (OCI-R; [10])

OCI-R is a self-report questionnaire of 18 items, and it measures OCD symptoms across six subscales: washing, checking, neutralising, obsessing, ordering, and hoarding. OCI-R was used in the initial screening of eligible participants, where the OCD subscale (which excludes the hoarding component) was used to determine participants who are at risk of developing OCD symptoms (cut off point (≥ 12). For the present study, the reduction in OCI-R OCD subscale assessment is the primary outcomes.

#### Patient Health Questionnaire-9 (PHQ-9; [20])

PHQ-9 is one of the most widely used measures of depression and it is based on the diagnostic criteria for major depressive disorder in the Diagnostic and Statistical Manual (DSM-IV; APA, 1994). Scores vary from 0 to 27, where a greater score indicates more severe depressive symptoms.

#### Generalized Anxiety Disorder-7 (GAD-7; [29])

GAD-7 measures symptoms of anxiety, based on the generalized anxiety disorder criteria in DSM-IV; APA, 1994). Respondents evaluate the level of their symptoms over the last two weeks and a cut-off score greater than 10 indicates further evaluation is recommended.

### Secondary outcome measures

#### Obsessive Beliefs Questionnaire (OBQ-44; [24])

OBQ-44 is a self-report scale that measures belief domains linked to OCD. The three subscales are (1) responsibility/threat estimation, (2) perfectionism/certainty, and (3) importance/control of thoughts. Answers are rated on a 7-point scale (1 = “disagree very much” to 7 = “agree very much”).

#### Automatic Thoughts Questionnaire (ATQ; Hollon & Kendall, 1980)

The Romanian version of ATQ [23] is a 15-item measure that evaluates self-reported negative thoughts. The questionnaire was developed to measure the most frequent negative thoughts and negative self-evaluations, typically associated with depression. Answers are rated on a 5-point scale (1 = “not at all” to 5 = “all the time”) and the total score ranges from 15 to 75.

#### Brief Experiential Avoidance Questionnaire (BEAQ; Gamez et al., 2014)

The BEAQ is a 15-item self-reports questionnaire that measures experiential avoidance. Items are rated on a 6-point Likert scale (1 = “strongly disagree” to 6 = “strongly agree”). Item 6 is a reversed item, and scores range from 15 to 90 points. Higher scores reflect higher experiential avoidance.

#### Intolerance of Uncertainty Scale (IUS; [5])

The IUS is a 27-item measure that evaluates how individuals relate to uncertainty. It contains items such as “Uncertainty makes me uneasy, anxious, or stressed”, “A small unforeseen event can spoil everything, even with the best of planning” and “When I am uncertain, I can’t go forward”. Answers are rated on a 5 points scale (1 = “not at all characteristics” to 5 = “entirely characteristic”)

#### General Health Questionnaire-12 (GHQ-12; [15])

The GHQ-12 consists of 12 items, each assessing the severity of a mental issue over the past few weeks. Answers are rated on a 4-point Likert scale, from 0 to 3. A total score of 36 can be generated, by rating the positive items from 0 (always) to 3 (never) and the negative ones from 3 (always) to 0 (never), so that a higher score indicate worse health.

#### Resilience Scale for Adults (RSA; [13])

The RSA is a 43-item measure with five factors: personal competence, social competence, family cohesion, social support, and personal organization. Answers are rated on a 5-point Likert scale from 1 = “not at all” to 5 = “a lot”).

#### WHO Quality of Life - BREF (WHOQOL-BREF; [28])

WHOQOL-BREF is one of the most widely used assessments of quality of life. In the current study, we will use the global item of the instrument (How would you rate your quality of life), answered on a 5-point Likert scale.

Post-intervention assessment will take place immediately after the intervention is completed and will include the same measures, as well as the Client Satisfaction Questionnaire-8 (CSQ-8; [21]). The assessments will be completed online, using the Qualtrics platform. We will also perform one follow-up assessment six months later, using the same measures and the Structured Clinical Interview for DSM-5 to compare the OCD diagnostic incidence.

### Statistical analyses

#### Data analysis

Demographic and clinical data will be reported as means and SDs for continuous parametric data, medians, and ranges for non-parametric data, and frequencies and percentages for categorical data. Only two authors will have access to the final trial dataset. To illustrate participant flow, we will report results in a CONSORT diagram. Data analysis will be conducted using SPSS for Windows version 25. Given the anticipated dropout rate, mixed models will be employed as the most suitable statistical method. This approach is well-suited for analyzing repeated measures, accounting for the dependency between observations and handling missing data effectively. Mixed models will be adjusted for baseline values of the repeated measures. Descriptive statistics will be generated to summarize the means and proportions of baseline clinical and demographic variables across treatment conditions, allowing for the assessment of potential imbalances. Fixed effects in the model will include time, treatment, and their interaction. In cases of missing data, these variables will also be included as fixed effects. The significance of the time*treatment interaction p-values for various outcome measures will be assessed using the Benjamini–Hochberg procedure (two-sided p < 0.05). Time will be treated categorically, with the first post-baseline measurement serving as the reference category. To address the correlation among repeated measurements, a first-order autoregressive (AR (1)) structure will be imposed on the residuals. Furthermore, the interaction effect between time and group will be explored by analyzing estimated marginal means at different time points. We anticipate a significant interaction effect between time and group, signifying differential changes in scores over time between the two treatment conditions. Specifically, we expect a more pronounced decline in scores over time in the prevention group compared to the control group. To assess the statistical significance of improvements in the treatment conditions, a least significant difference test will be conducted with estimated marginal means to compare changes between groups. Linear mixed models are expected to reveal a statistically significant decline in the prevention condition from pretest to post-test, with no significant differences between post-test and follow-up measures. To facilitate comparisons with other studies, Cohen’s d statistic will be calculated to determine within-group effect sizes. In cases where the proportion of missing data exceeds 10%, maximum likelihood imputations will be performed based on demographics and pretreatment scores. Additionally, the proportions of dropouts and diagnostic incidence (from pre-test to follow-up) in the two treatment groups will be compared using the chi-square test.

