### Specific contents of the ØCD prevention protocol

The program involves six sessions and includes established components of CBT [4] and ERP [11], namely: (1) psychoeducation and encouragement to reduce, change, or eliminate anxiety-reducing rituals (1 session), (2) cognitive restructuring by challenging dysfunctional beliefs (2 sessions), (3) behavioral changes by prolonged, imaginal and real-life exposure to distress-provoking stimuli (2 sessions), (4) addressing ways and skills to reduce relevant risk factors (i.e. fear of COVID-19) and to develop resilience factors (i.e. resilience levels, coping skills) and summary and recapitulation (1 session). The six sessions of the 2 weeks program correspond to three treatment modules (3 hours/module). An overview of the content covered in each stage is provided in Table 1.

**Table 1 Tab1:** Description of the ØCD modules and sessions

Module	Session	Session Content
Psychoeducation	Overview of OCD	• • Elicit from participant their understanding of OCD. • • Increase motivation for change through psychoeducation. • • Explain what OCD is and the forms it can take. • • Homework: monitor OCD-related thoughts, feelings, and behaviors.
1. Cognitive approach	2. Identifying obsessive sequences	• Mindfulness exercise (Body Scan) to ensure a relaxed state. • Homework debriefing. • Explain how obsessive sequences take place based on participants’ examples. • Connect obsessive sequences to their corresponding compulsions. Homework: identify obsessive sequences in everyday life.
2. Cognitive approach	3. Perspective and how to change it	• Homework debriefing. • Introduce the concept of perspective. • Explain how perspective can affect the formation and maintenance of the circle of obsessions. • Offer examples as to how changing the perspective can prevent engaging in the obsessive sequence and compulsions. • Introduce the Cognitive ABC model. • Homework: identify three cognitions and apply the Cognitive ABC model.
2. Behavioral approach	4. Exposure and Response Prevention (ERP)	• Homework debriefing. • Revision of the concepts discussed previously. • Discussion about compulsions. • Introduce Exposure and Response Prevention. • Engage participants in an ERP exercise. • Homework: choose a medium-level anxiety situation and apply the ERP steps.

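### One residual variance and, on the plain reading, one baseline slope for two visits months apart: arm contrasts at each visit are miscalibrated if variance or baseline correlation changes between them

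*Protocol article*

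**What the plan says.** The mixed model is set out in the protocol article, Statistical analyses, Data analysis:

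- Baseline: "Mixed models will be adjusted for baseline values of the repeated measures".
- Fixed effects: "Fixed effects in the model will include time, treatment, and their interaction". A baseline-by-time term is neither named nor excluded.
- Time: "Time will be treated categorically, with the first post-baseline measurement serving as the reference category". The modelled visits are therefore most naturally post-test and follow-up.
- Residuals: "a first-order autoregressive (AR (1)) structure will be imposed on the residuals".
- Inference: the time-by-treatment p-values of the outcomes are judged by Benjamini–Hochberg at two-sided 0.05. In addition, "the interaction effect between time and group will be explored by analyzing estimated marginal means at different time points", and a least significant difference test on those means compares change between the arms.

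The programme lasts two weeks (Specific contents of the ØCD prevention protocol), and post-test follows at once. Follow-up is six months later according to the end of the outcome measures section, and one year later according to the Abstract. The Abstract also names a MANOVA; this point concerns only the mixed model.

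**The concern.** Baseline usually predicts a score two weeks later better than one taken 6 to 12 months later. It then removes more variance at post-test than at follow-up, and the residual variances differ. A model with one residual variance averages them. The standard error comes out too large at post-test and too small at follow-up, and the liberal error falls on the visit that matters most for prevention.

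A second effect concerns the interaction. With the first post-baseline visit as reference, time-by-treatment compares the arms on the change from post-test to follow-up. A baseline term with the same slope at both visits drops out of that change, so the adjustment brings this test no precision.

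The visit contrasts may carry much of the efficacy claim. The plan expects the prevention arm to hold steady after post-test, so benefit may already be present at the reference visit, where this interaction cannot show it.

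**Working it through.** **Inputs.** The model terms and visit times are those in the article. It gives no correlations or visit SDs and no figure on this point to reproduce; the sample-size statement does not enter. The following are assumptions: r01 (baseline, post-test) 0.6–0.8, r02 (baseline, follow-up) 0.4–0.7, r12 (post-test, follow-up) 0.4–0.6, and s = follow-up SD / post-test SD, 1.0–1.2. Baseline and post-test SD are set to 1.

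**Step 1: AR(1) with two visits.** It has one variance and one correlation, so equal residual variance is forced.

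**Step 2: visit contrasts, complete data, one slope.**

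- Common slope: b = (r01 + s·r02)/2
- Residual variances: v1 = 1 − 2b·r01 + b²; v2 = s² − 2b·s·r02 + b²
- Pooled: v = (v1 + v2)/2
- Model SE / true SE at visit j: k_j = √(v/v_j)
- Type I error: 2[1 − Φ(1.96·k_j)]

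For 0.7/0.4/0.5 and s = 1: b = 0.55; v1 = 1 − 0.77 + 0.3025 = 0.5325; v2 = 1 − 0.44 + 0.3025 = 0.8625; v = 0.6975. Then k1 = √(0.6975/0.5325) = 1.14 and k2 = √(0.6975/0.8625) = 0.90, giving about 2.5% and 7.8%.

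For 0.6/0.5/0.6 and s = 1: b = 0.55; v1 = 1 − 0.66 + 0.3025 = 0.6425; v2 = 1 − 0.55 + 0.3025 = 0.7525; v = 0.6975. Then k1 = 1.04 and k2 = 0.96, giving about 4.1% and 5.9%.

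**Step 3: interaction.** With one slope, the variance of the post-test-to-follow-up change is 1 + s² − 2s·r12, the same as with no baseline covariate. A baseline-by-time term lowers it by (r01 − s·r02)². For 0.7/0.4/0.5: from 1.00 to 1.00 − 0.09 = 0.91, a 9% cut. For 0.6/0.5/0.6: from 0.80 to 0.79, about 1%.

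| r01 / r02 / r12 | s | v1, v2 | k1, k2 | Type I error, post-test / follow-up | Interaction variance forgone |
|---|---|---|---|---|---|
| 0.6 / 0.6 / 0.6 | 1.0 | 0.640, 0.640 | 1.00, 1.00 | 5.0% / 5.0% | 0% |
| 0.6 / 0.5 / 0.6 | 1.0 | 0.643, 0.753 | 1.04, 0.96 | 4.1% / 5.9% | 1% |
| 0.7 / 0.5 / 0.5 | 1.0 | 0.520, 0.760 | 1.11, 0.92 | 3.0% / 7.2% | 4% |
| 0.7 / 0.4 / 0.5 | 1.0 | 0.533, 0.863 | 1.14, 0.90 | 2.5% / 7.8% | 9% |
| 0.8 / 0.4 / 0.4 | 1.0 | 0.400, 0.880 | 1.27, 0.85 | 1.3% / 9.5% | 13% |
| 0.6 / 0.6 / 0.6 | 1.2 | 0.644, 0.925 | 1.10, 0.92 | 3.0% / 7.1% | 1% |

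**Step 4: simulation** (REML, 100 per arm, 2,000 runs, 0.7/0.4/0.5, s = 1).

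- Complete data: interaction estimate and SE with one slope equal those with no baseline (largest differences 3e-16 and 3e-7). The interaction SE is sound: empirical 0.139, model 0.141, rejection 4.3%. The visit contrasts reject 2.5% and 7.7%.
- Follow-up dropout of 12.5% (200 recruited for 175): interaction model SE is 0.1467 with one slope and 0.1486 with no baseline, with empirical SEs of 0.1515 and 0.1514. Interaction rejection is 6.0%; the visit contrasts reject 2.4% and 9.0%.
- Baseline-by-time added but AR(1) kept, complete data: interaction empirical SE falls to 0.133, but the visit contrasts still reject 2.8% and 7.7%.

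**The case against.** Four objections carry weight.

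- **The single slope is inferred.** The article does not say that baseline has one slope. Its list of fixed effects is not exhaustive, since baseline itself is not on it, and a fuller plan may hold a baseline-by-time term. This stands as a caution on the slope half. It does not touch AR(1), which is stated.
- **The size rests on assumptions.** A reader might infer that the standard errors at both visits are wrong. The documents do not support that: they give no correlations or SDs, and with both equal across visits the error is 5%. Entry at OCI-R ≥ 12 also restricts the early range of that outcome and would tend to lower its baseline correlations, so 0.8 is optimistic there.
- **The controlled test is sound.** A reader might infer that the Benjamini–Hochberg results are invalid or that baseline adjustment does nothing. With two complete visits the interaction SE is valid and only efficiency is lost. The cancellation of baseline is exact only with complete data, and the trial expects dropout. Adjustment still improves precision at each visit.
- **Baseline may be an outcome row.** The section also expects a decline from pretest to post-test. If pretest is modelled as a third repeated measure, the cancellation argument does not apply in this form. AR(1) would still impose one variance, and would also tie the correlations together across very unequal gaps.

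**Conclusion.** The point holds conditionally. The stated AR(1) forces one residual variance on two visits months apart. If baseline correlation or outcome SD changes between them, the arm contrast is conservative at the visit with the smaller residual variance and liberal at the other; under the assumptions used, that means conservative at post-test and liberal at follow-up. Where the residual variances differ, type I error runs from about 4% and 6% in the mildest case to 1.3% and 9.5% in the most adverse. On the plain reading of one slope, the interaction test also forgoes 0–13% of its variance, exactly so with complete data and approximately with dropout. This is a cheap safeguard for the visit contrasts and a small precision gain for the interaction, not a demonstrated error in the controlled test.

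**What to change.** In the Data analysis section:

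1. Replace AR(1) with an unstructured residual covariance. With two post-baseline visits, heterogeneous AR(1) amounts to the same thing.
2. Add baseline-by-time to the fixed effects of every outcome model.
3. Report the between-arm estimated marginal means at each visit from that model.
4. Say whether pretest is a covariate or an outcome row. If it is an outcome row, unstructured is the safer choice, because heterogeneous AR(1) would still constrain the correlations.

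The first two changes do different jobs. The covariance calibrates the visit contrasts, which baseline-by-time alone does not do; baseline-by-time gives the interaction its precision.

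With two visits the cost is one extra variance and one extra slope per model, a sentence or two of text, and no new data. With three outcome rows, unstructured has six covariance parameters against two for AR(1), four more. According to Trial status, analysis was to start only once the primary endpoint data were complete, so at submission the change could still be made before results were seen.
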